### Study procedures and data collection

Baseline data (including demographics, comorbidities, medication use, cholesterol levels, and sociodemographic variables) will be collected by research personnel using a standardized abstraction instrument at the time of the patient's catheterization. The primary source of outcome data for the study will be patient self-report on telephone contact at three and six months, with cross-referencing to pharmacy records for medications, centralized laboratory data for fasting lipid panels, and medical records for clinical outcomes. In an earlier study, we found a high degree of agreement between patient self-report of statin and ACE inhibitor use and data from dispensing pharmacies (simple agreements ranged between 88% to 99% and kappas were 0.78 to 0.93)[83]. Vital status will be queried via the APPROACH database. The outcome data will be abstracted using standardized forms in a secure database housed in the Epidemiology Coordinating and Research (EPICORE) Centre, University of Alberta, Canada.

Investigators, outcome assessors, and study patients will be masked to allocation status. Primary care physicians cannot be blinded to allocation status. Follow-up data will be collected without knowledge of allocation status in an independent and blinded fashion, and statistical analyses will be conducted by a statistician blinded to allocation status.

### Sample size

In a survey of 22 members of the divisions of cardiology and general internal medicine at the University of Alberta, we determined that the "minimal" clinically important difference for this particular intervention to be considered useful was a 15% absolute improvement over and above usual care. After six months, we estimate that no more than 20% of control patients will have attained our composite primary outcome, given that patients who are already on a statin and have optimal LDL cholesterol levels will be excluded from this study at baseline. We calculated our sample size to detect a 15% absolute increase in the primary outcome, set the α error rate at 0.05 (2-sided), and the β error at 0.20 (power 80%) – this yielded a sample size of 138 patients per study arm. Allowing for losses during follow-up, the ability to examine each of the conditions separately, and the possibility of a very small design effect associated with patient clustering, the total sample size has been adjusted upwards to 160 patients per arm (480 in total).

### Statistical analyses

Intention-to-treat analyses will be carried out with patients as the unit of analysis. Although the physician will be the unit of allocation, we anticipate a very small design effect, and the outcomes for individual patients will be clinically and statistically independent of each other.

The primary outcome will first be tested using the chi square statistic to compare the attainment of our primary statin outcome within six months in patients randomized to the Local Opinion Leader Statement versus patients randomized to the Unsigned Evidence Statement. If the impact of the Local Opinion Leader Statement is significantly different from that of the Unsigned Evidence Statement, we will compare each to usual care separately. If the impact of the Local Opinion Leader Statement and the Unsigned Evidence Statement are similar, we will combine data from both arms and compare this with usual care, which will essentially be a test of point-of-care reminders versus usual care.

In order to investigate what factors are associated with changes in the primary outcome (our dependent binary variable), and to control for the possibility of potential imbalances in patient-level characteristics at baseline, multivariable logistic regression analyses will be used to examine those variables that are deemed to be clinically important (i.e., age, gender) or that differ statistically at a p-value < 0.10 between study arms. In addition, to examine the possibility of "cluster-associated" study design effects, two sensitivity analyses will be considered. First, the main analysis will be repeated using the physician as the unit of analysis. Second, the aforementioned logistic regression models will be reanalyzed using generalized estimating equations to control for the potential lack of statistical independence among patients treated by the same study physician[84].

There will be one pre-planned interim analysis to explore event rates in all three study arms after 80 patients per arm have reached the six month primary outcome time-point. We are primarily interested in examining whether projected event rates are correct, or whether the sample size will need to be adjusted upwards, and will employ the Haybittle-Peto stopping rule using a Z value of 3.0 for this interim test. For the main study analysis, we will consider a p-value < 0.05 to be statistically significant.

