## Methods

### Study design

The study design is a randomized clinical trial testing three different intervention policies: Usual care versus Local Opinion Leader Statement versus Unsigned Evidence Statement (see Trial Flow in Figure 1). The target population is patients with CAD proven on coronary angiography. As there is a potential for a physician or a group practice of physicians to have patients randomized to more than one arm of the study, cluster randomization at the level of the practice will be employed to avoid contamination. [79] Thus, this represents the optimal design for evaluating quality improvement interventions[80].

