### Allocation to experimental arms

Randomization will take place 1:1:1 at the level of the practice (either individual physician for solo practitioners or clinic for those physicians who practice in a group setting) following the completion of the patient's coronary angiogram using a 'real-time' central randomization system with allocation concealment embedded in the APPROACH software. After a practice's first patient is randomized, all subsequent patients from that practice will be assigned to whatever treatment arm the first patient was randomized to.

While this is a form of cluster randomization, we anticipate the design effect to be negligible since the majority of physicians will contribute no more than one or two study patients, and thus all sample size and analytic considerations use the patient as the unit of analysis and the unit of causal inference.

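### Practices are randomised, but the primary test is an unadjusted patient-level chi-square resting on an independence claim that the protocol itself contradicts

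*Protocol article*

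**What the plan says.** - **Unit randomised.** Under Study design, "cluster randomization at the level of the practice will be employed to avoid contamination". The allocation section is more specific: "Randomization will take place 1:1:1 at the level of the practice (either individual physician for solo practitioners or clinic for those physicians who practice" together, so a group clinic counts as one unit. Later patients follow the first one: "all subsequent patients from that practice will be assigned to whatever treatment arm the first patient was randomized to".
- **Unit analysed.** The Allocation section goes on to say that "all sample size and analytic considerations use the patient as the unit of analysis and the unit of causal inference". Its reason is that the design effect should be negligible because most physicians will supply only one or two patients. Statistical analyses repeats the choice: "Intention-to-treat analyses will be carried out with patients as the unit of analysis".
- **Test.** Statistical analyses states that "The primary outcome will first be tested using the chi square statistic", with significance at p < 0.05.
- **Justification.** The same section says "Although the physician will be the unit of allocation, we anticipate a very small design effect". It goes further and asserts that "the outcomes for individual patients will be clinically and statistically independent of each other".
- **Clustering elsewhere.** Statistical analyses lists two sensitivity analyses. One repeats the main analysis with the physician as the unit. The other refits the covariate-adjusted logistic models by generalized estimating equations (GEE), to handle possible dependence among one physician's patients. The Sample size section names a very small design effect among three reasons for going from 138 to 160 per arm.

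**The concern.** A chi-square on patients is valid in a cluster-randomised trial only if the design effect is 1. The protocol asserts that condition as a fact, but the rest of the text does not treat it as one: GEE and a design-effect allowance would both be unnecessary if outcomes were independent.

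The cluster-size argument does not close the gap, for two reasons. It counts physicians, whereas the randomised unit may be a clinic that pools several physicians. And a majority of small clusters sets no limit on the larger ones, which weigh most in the design effect.

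Both sensitivity analyses also use the physician, so in group practices neither matches the randomised unit.

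At stake is the confirmatory claim. Significance is declared on the unadjusted test, and nothing is said about what follows if a sensitivity analysis disagrees. The same variance would enter the interim test (Z of 3.0) and the secondary outcomes, which are to use similar methods.

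**Working it through.** **1. Reproduce the plan's figure.** Inputs from the Sample size section: 20% versus 35%, two-sided α 0.05, power 80%. With pooled variance under the null and no continuity correction:

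n = [1.96·√(2·0.275·0.725) + 0.8416·√(0.20·0.80 + 0.35·0.65)]² / 0.15² = (1.2377 + 0.5239)² / 0.0225 = 137.9, so 138 per arm.

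This matches exactly, with a design effect (DE) of 1. Power at 160 per arm is 85.5% if DE = 1.

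**2. What 160 covers.** 160/138 = 1.159. That absorbs a DE of 1.16 with no losses, 160·0.95/138 = 1.10 with 5% losses, or 160·0.90/138 = 1.04 with 10% losses (loss rates assumed). This is headroom for power. It leaves the chi-square's standard error, and hence its type I error, uncorrected.

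**3. Actual error rate of the unadjusted test.** The protocol gives no ICC and no practice-size distribution, so both are assumed.

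- DE = 1 + (m_A − 1)·ICC, where m_A = E[m²]/E[m] = mean·(1 + CV²)
- Actual α = 2·[1 − Φ(1.96/√DE)]
- Factor by which a valid standard error exceeds the unadjusted one = √DE
- n per arm for 80% power = 138·DE; power at 160 is taken at an effective size of 160/DE

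Practices of one or two patients in equal numbers: m_A = (1 + 4)/(1 + 2) = 1.667. Mean three patients with CV 0.8: m_A = 3·1.64 = 4.92.

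| Practice sizes (assumed) | ICC | DE | Actual α | √DE | n per arm needed | Power at 160 |
|---|---|---|---|---|---|---|
| All one patient | any | 1.00 | 5.0% | 1.00 | 138 | 86% |
| One or two, equal numbers | 0.05 | 1.03 | 5.4% | 1.02 | 143 | 84% |
| One or two, equal numbers | 0.10 | 1.07 | 5.8% | 1.03 | 148 | 83% |
| Mean 3, CV 0.8 | 0.05 | 1.20 | 7.3% | 1.09 | 166 | 79% |
| Mean 3, CV 0.8 | 0.10 | 1.39 | 9.7% | 1.18 | 193 | 72% |

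The power column is for a test with the correct variance and no losses.

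**4. Simulation check.** Beta-binomial outcomes were simulated at 20% in both arms, 160 patients per arm, and tested by plain chi-square. One patient per practice gave 4.8–5.0%. One or two patients gave about 5.3–6.0% over ICC 0.05–0.10. Mean 3 with CV near 0.8 gave 6.3–7.1% at ICC 0.05 and 9.4–9.5% at ICC 0.10. Formula and simulation together span about 5.3–6.0% and 6.3–9.7% for the two multi-patient scenarios.

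**5. Does a majority of small clusters guarantee a negligible effect?** Take a geometric size distribution with mean 3 (CV 0.82). The share of clusters with at most two patients is 1 − (2/3)² = 56%, so a majority is small. Yet clusters of five or more hold (2/3)⁴·7/3 = 46% of patients. A majority at one or two is therefore compatible with a DE of 1.2 to 1.4.

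**The case against.** The best defence is that the bias may be trivial and that the protocol is open about clustering. On a literal reading of its picture, one or two patients per practice, the error rate rises only to between 5 and 6%. The mean-of-three scenario meets the majority premise only narrowly. Clustering is acknowledged in several places. Although the sensitivity analyses are introduced as something to be considered, the sentences that follow describe them in firm terms, and GEE is named. All of this stands. It limits the size of the problem and rules out saying that clustering is ignored, but it does not make the unadjusted test valid.

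A reader might infer more than the text supports:

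- **That outcomes within a practice are correlated by construction.** The primary outcome credits action by any of the patient's physicians, not only the randomised practice. Correlation is plausible, but its size is an empirical matter.
- **That the contamination rationale contradicts independence.** Contamination concerns exposure to more than one arm's material. It does not imply correlated outcomes within an arm. The real contradictions are with the GEE rationale and the design-effect allowance.
- **That confidence intervals are misstated.** The Statistical analyses section specifies none. The point reaches only intervals that might be built on the same variance.
- **That the planned GEE only needs promoting.** It clusters on physician and carries covariates chosen partly by baseline p < 0.10, so it is not the practice-level comparison needed here.

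**Conclusion.** The primary test is wrong as written. It does not respect the randomised unit, and the independence claim behind it conflicts with the same section and with the sample size section. The direction is certain for any positive ICC when some practices contribute more than one patient: p-values are too small. The size cannot be fixed from the document. Under an assumed ICC of 0.05 to 0.10, the nominal 5% becomes about 5.3–6.0% with one or two patients per practice in equal numbers, and about 6.3–9.7% with mean 3 and CV 0.8. With one patient per practice there is no inflation. A claim that the trial's error rate is seriously inflated would need practice sizes and an ICC that the protocol does not give.

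**What to change.** - Make every primary-outcome comparison cluster-respecting, including the first contrast of the two statements and whichever comparison with usual care follows. Use either logistic GEE with an arm term, the randomised practice as cluster and robust standard errors, or a cluster-adjusted chi-square.
- Use the same method for the interim test and the secondary outcomes.
- Keep the plain chi-square as a supportive result.
- In the planned covariate-adjusted GEE, change the clustering unit from physician to practice. Make the analysis section's description of the allocation unit agree with the Allocation section.
- Delete the sentence claiming independence. State the ICC and practice sizes assumed in moving from 138 to 160.

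**Cost.** Little extra analysis work, provided a practice identifier is kept for each patient. Standard errors rise by √DE: about 2–3% with one or two patients per practice, and up to about 18% at a DE of 1.39. If clustering is negligible, results barely move. If it is material, the power actually delivered at 160 per arm falls, to about 72% in the last row of the table, and the sample size would need another look.

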#### Aim of the study

This trial is designed to test two interventions for improving the quality of care for patients with established CAD. The principal hypothesis to be tested is: Does a local opinion leader-based quality improvement intervention influence primary care physicians to increase the provision of secondary prevention therapies in their patients with known CAD compared to usual care? The secondary hypotheses to be tested are: (1) Does the same quality improvement intervention, but without explicit local opinion leader endorsement (i.e., without the local opinion leaders' signatures), improve the provision of secondary prevention maneuvers in CAD patients compared to usual care? And, (2) does local opinion leader endorsement increase the effectiveness of the quality improvement intervention?

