#### Primary outcome

The primary outcome measure is a composite measure representing improvement in statin-related secondary prevention consisting of: 1) provision of a statin sample, or 2) provision of a statin prescription, or 3) increasing the dosage of a statin within the first six months post-angiogram. As this is a composite end-point, only the first event attained in the cluster will be counted for analysis, although all events will be recorded in the database.

Six months was chosen for the primary and secondary outcomes because the average number of physician visits in our audit of trial-eligible patients attending the University of Alberta cardiac catheterization laboratory in the 2003 year was 1.8 visits in six months. As we are assessing the impact of the Local Opinion Leader Statement and Unsigned Evidence Statement on physician practice patterns, for the purposes of this study we are interested solely in evaluating attempted practice change. In other words, if a patient is provided with a statin sample or a statin prescription, or the dosage is increased by any of the patient's physicians, it would still count as a positive outcome for the main study analysis, even if the patient cannot tolerate the medication and discontinues it or is noncompliant during follow-up. We recognize that patient (and physician) long-term compliance with preventive therapies is important, and will collect data on persistence rates with secondary prevention maneuvers over the six months of the study. We anticipate that this data will serve as pilot data for a planned future study on interventions to improve provider/patient persistence rates.

We will examine the primary outcome rates in all three treatment arms as follows: the primary comparison will be between those patients randomized to the Local Opinion Leader Statement versus usual care, and the secondary comparisons will be (a) between those patients randomized to the Unsigned Evidence Statement versus usual care, and (b) between those patients randomized to the Local Opinion Leader Statements versus Unsigned Evidence Statements.

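### The analysis section runs the declared primary comparison (signed statement versus usual care) only if signed versus unsigned is significant; otherwise it pools the two statement arms

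*Protocol article*

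**What the plan says.** Three sections of the protocol agree on the main question.

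- Aim of the study: the principal hypothesis asks "Does a local opinion leader-based quality improvement intervention influence primary care physicians to increase the provision of secondary prevention therapies", with usual care as the comparator. The unsigned statement's effect and the added value of endorsement are secondary hypotheses.
- Primary outcome: "the primary comparison will be between those patients randomized to the Local Opinion Leader Statement versus usual care". The secondary comparisons are (a) unsigned versus usual care and ("b) between those patients randomized to the Local Opinion Leader Statements versus Unsigned Evidence Statements".
- Sample size: 138 patients per arm, raised to 160, to detect a 15-point absolute gain over a usual-care rate of at most 20%.

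The Statistical analyses section follows a different order. "The primary outcome will first be tested using the chi square statistic to compare the attainment of our primary statin outcome within six months", and the two arms named in that sentence are the signed and unsigned statements. If they differ significantly, "we will compare each to usual care separately". If not, "If the impact of the Local Opinion Leader Statement and the Unsigned Evidence Statement are similar, we will combine data from both arms" and set them against usual care, "which will essentially be a test of point-of-care reminders versus usual care". No margin or criterion for similar is given. Nothing says that signed versus usual care is also run when the arms are pooled. The Other analyses section carries similar methods over to the secondary outcomes.

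**The concern.** A comparison declared secondary decides whether the declared primary comparison is carried out at all. An analyst who follows the Primary outcome section and one who follows the Statistical analyses section can report different primary results from the same data, and the choice between them could be made after the data are seen.

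The rule also appears to treat a non-significant difference between two active statements as evidence that they are alike. The trial was sized for 15 points over usual care. Any gap between signed and unsigned is smaller than that unless the unsigned statement does nothing, so non-significance there is weak evidence of similarity. Once the arms are pooled, the result concerns reminders in general, and a positive result credits both statements even if only one works.

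**Working it through.** **Inputs.** From the Sample size section: usual care 20%, signed 35% (20% plus 15 points), two-sided α 0.05, 138 per arm calculated and 160 planned. From Statistical analyses: the staged rule and p < 0.05. Assumed: an unsigned rate between 20% and 35%, because the protocol gives none; similar read as p ≥ 0.05; patients independent; 160 per arm all analysed; no interim look.

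**1. The plan's own figure.** Two proportions, pooled variance under the null, no continuity correction:

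n = [1.96·√(2·0.275·0.725) + 0.8416·√(0.20·0.80 + 0.35·0.65)]² / 0.15²
= (1.96·0.6315 + 0.8416·0.6225)² / 0.0225 = 137.9, so 138 per arm. Reproduced. Power for 20% versus 35% is 80.0% at 138 per arm and 85.5% at 160 (86% by simulation).

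**2. Chance that the first test is significant.** With d the signed-minus-unsigned difference, p̄ the mean of the two rates and n = 160:

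power = Φ[(d − 1.96·s₀)/s₁], where s₀ = √(2p̄(1−p̄)/n) and s₁ = √((p₁(1−p₁)+p₂(1−p₂))/n).

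- Unsigned 20%: (0.150 − 1.96·0.04992)/0.04921 = 1.06, giving 0.855
- Unsigned 25%: (0.100 − 1.96·0.05123)/0.05093 = −0.01, giving 0.497
- Unsigned 27.5%: (0.075 − 1.96·0.05182)/0.05165 = −0.51, giving 0.303
- Unsigned 30%: (0.050 − 1.96·0.05237)/0.05229 = −1.01, giving 0.157

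**3. The staged rule by simulation** (400,000 trials per scenario, uncorrected chi-square, 160 per arm, usual care 20%, signed 35%):

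| Unsigned rate | Arms pooled, primary comparison skipped | Primary comparison run and won | Pooled test positive | Sum of the last two |
|---|---|---|---|---|
| 20% | 0.141 | 0.772 | 0.057 | 0.829 |
| 25% | 0.501 | 0.473 | 0.327 | 0.800 |
| 27.5% | 0.695 | 0.295 | 0.524 | 0.819 |
| 30% | 0.840 | 0.155 | 0.701 | 0.856 |
| 35% | 0.949 | 0.037 | 0.888 | 0.925 |

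Signed versus usual care, always run, is won in 0.859 of trials in every row. With 138 per arm the skipped proportions for the first four rows are 0.196, 0.558, 0.731 and 0.858.

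**4. Wrong claims.** If the signed rate is 35% and the unsigned statement has no effect (20%), the unsigned statement is still credited in about 0.057 (pooled win) + 0.012 (separate win) = 0.069 of trials, against a nominal one-sided 0.025. If the signed rate is 30%, the figure is about 0.10. With all arms at 20%, at least one rejection against usual care occurs in 0.066 of trials.

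**The case against.** Four points deserve a fair hearing.

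**How often the primary comparison is lost.** A reader might infer that the principal hypothesis is usually replaced. The documents do not support that, because the unsigned rate is not stated. The Background reports little or no gain in statin prescribing from unendorsed reminders, and the protocol says that the unsigned arm essentially repeats those studies. On that premise the unsigned rate could be close to 20%, where the comparison is skipped in about 14% of trials. Skipping reaches about half only when the unsigned statement achieves a third of the signed effect (5 of 15 points).

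**Messenger and message.** A reader might infer that the plan can no longer separate the two. It can: signed versus unsigned is tested in every trial. Only the pooled test fails to separate them, and the protocol says openly what that test is.

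**Power and error.** A reader might take the fall from 86% to as little as 15% as lost power. If a positive pooled test also counts as a success, the chance is 80% to 86% in the first four rows, at most about 6 points below the direct test. A reader might also quote a 9.7% error rate when no arm has an effect. That figure counts the first test itself; false rejections against usual care are about 6.6%.

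**The meaning of similar.** A margin could sit in an analysis plan that is not shown, so reading it as p ≥ 0.05 is an inference, though a natural one from the preceding sentence.

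These points limit the size of the problem. None reconciles the two sections: the pooled test answers a different question, and under any definition of similar the pooled branch does not provide for the declared primary comparison.

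**Conclusion.** The contradiction stands on the text alone. The Aim and Primary outcome sections make signed versus usual care primary and the Sample size section sizes the trial for a gain over usual care, while Statistical analyses makes that comparison conditional on a secondary one. Under the assumptions above, the declared comparison is skipped in about 14% to 84% of trials as the unsigned rate goes from 20% to 30%, and is run and won in about 77% down to 15%, against 86% if always run. The effect on false claims is moderate: about 7% wrongly credit an inert unsigned statement (10% if the signed rate is 30%), and about 6.6% give a false rejection against usual care when nothing works. The figures ignore clustering and losses to follow-up, so they are approximate.

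**What to change.** In Statistical analyses, replace the staged rule as follows.

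1. Always run signed statement versus usual care as the primary test at two-sided 0.05, not conditional on any other result.
2. Run unsigned versus usual care and signed versus unsigned as the two separate secondary comparisons already listed under Primary outcome, neither gated on the other. Report the signed-minus-unsigned difference with its 95% confidence interval instead of declaring the arms similar.
3. Keep the pooled comparison with usual care only as a labelled supportive analysis.

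The secondary comparisons should not be chained with signed versus unsigned last. If that test required both earlier ones to succeed, it would be reached and won in only about 1% of trials when the unsigned rate is 20% and 4% when it is 25%, against 86% and 50% when it is run in every trial.

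The change is wording only, with no extra patients. The cost is the pooling gain when the two statements are equally effective: about 93% (0.037 + 0.888 = 0.925) under the staged rule, against 86% for the direct test.

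### Practices are randomised, but the design-effect argument and both clustering sensitivity analyses are defined by physician, so they can under-correct in group clinics

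*Protocol article*

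**What the plan says.** The Protocol article describes the randomised unit in two ways.

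- **Practice.** Study design says that "cluster randomization at the level of the practice will be employed to avoid contamination". Allocation to experimental arms repeats this ("Randomization will take place 1:1:1 at the level of the practice") and defines a practice as "either individual physician for solo practitioners or clinic for those physicians who practice in a group setting". Once a practice's first patient is randomised, its later patients follow into the same arm.
- **Physician.** The Abstract places the cluster randomisation at the level of the primary care physician. Statistical analyses opens its clustering argument with "Although the physician will be the unit of allocation".

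The physician is also the unit wherever clustering is dealt with:

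- Allocation to experimental arms calls the design effect negligible because "the majority of physicians will contribute no more than one or two study patients", and on that ground takes the patient as the unit for sample size and analysis.
- Sample size raises 138 per arm to 160 to cover losses, separate examination of each condition and "the possibility of a very small design effect associated with patient clustering". It gives no ICC, cluster size or loss rate.
- Statistical analyses uses an unadjusted chi-square for the primary outcome and offers two sensitivity analyses. One repeats the main analysis by physician. The other is a GEE to "control for the potential lack of statistical independence among patients treated by the same study physician".

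No analysis is defined by practice.

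**The concern.** In a cluster-randomised trial, the variance of the treatment comparison depends on the correlation among all patients who were allocated together. In a group clinic that set includes the patients of every physician in the clinic. A GEE with physician as cluster allows for correlation within each physician's patients and assumes none between colleagues in the same clinic. If that correlation is positive, the standard error is too small.

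The protocol itself treats clinic colleagues as linked: Study design gives contamination within a group practice as the reason for randomising whole practices. It then treats them as independent in the analysis.

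The primary chi-square ignores clustering, so the two sensitivity analyses are its only check. If they are built on a unit that was not randomised, they can look reassuring without testing the right thing. The design-effect argument has the same fault, because the relevant count is patients per practice, not per physician.

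**Working it through.** **1. The plan's own figure.** Inputs from Sample size: 20% v 35%, two-sided alpha 0.05, power 80%. Pooled-variance formula without continuity correction:

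n = [1.960·√(2·0.275·0.725) + 0.842·√(0.20·0.80 + 0.35·0.65)]² / 0.15² = 137.9, so 138 per arm.

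The stated 138 is reproduced. With 160 per arm, no loss and no clustering, power is 85.5%.

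**2. What the 22 extra patients can absorb.** The largest design effect (DE) that keeps 80% power is the number analysed divided by 138. Loss rates are assumptions.

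- No loss: 160/138 = 1.16
- 5% loss: 152/138 = 1.10
- 10% loss: 144/138 = 1.04

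**3. How the unit changes the design effect.** DE = 1 + (m − 1)·ICC, where m is patients per cluster. Both m and ICC (0.05 to 0.10) are assumptions. The row m = 1.5 represents the plan's one or two patients per physician; m = 3 to 5 represents possible practice sizes.

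| m | DE | Needed per arm, no loss | Power at 160, no loss | Power at 160, 5% loss |
|---|---|---|---|---|
| 1.5 | 1.025–1.05 | 142–145 | 84.7–83.8% | 82.8–81.9% |
| 3 | 1.10–1.20 | 152–166 | 82.1–78.6% | 80.1–76.5% |
| 4 | 1.15–1.30 | 159–180 | 80.3–75.3% | 78.3–73.2% |
| 5 | 1.20–1.40 | 166–194 | 78.6–72.2% | 76.5–69.9% |

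Without losses, 160 per arm holds 80% power up to an ICC of about 0.08 (m = 3), 0.053 (m = 4) or 0.040 (m = 5). After 5% loss the limits are about 0.051, 0.034 and 0.025.

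Unequal practice sizes raise the design effect: DE = 1 + (m(1 + CV²) − 1)·ICC. For m = 3 and CV 0.8 (both assumed), this is 1 + 3.92·ICC = 1.20 to 1.39.

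**4. Type I error of a test clustered on physician.** The approximation is 2·[1 − Φ(1.96·√(DE by physician / DE by practice))], with equal correlation among all patients of a practice.

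- *Every patient in a clinic giving four patients of four physicians.* DE by physician is 1 and DE by practice is 1 + 3·ICC = 1.15 to 1.30. Type I error is 6.8% to 8.6%. The physician-level GEE sees only single-patient clusters and corrects nothing, so the unadjusted chi-square has the same error.
- *Half the patients in such clinics, the rest in solo or single-patient practices.* Average DE is 1 + 0.5·3·ICC = 1.075 to 1.15; error 5.9% to 6.8%. At one quarter it is 5.4% to 5.9%.
- *1.5 patients per physician throughout.* Error is 5.9% to 6.7% (m = 3), 6.4% to 7.8% (m = 4) and 7.0% to 9.0% (m = 5). At ICC 0.02 it is 5.3% to 5.8% for m = 3 to 5.
- *Solo practitioners only.* Physician and practice are the same unit, so using the physician causes no under-correction.

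**The case against.** **Loose wording.** Physician may be shorthand for practice, since a practice is a single physician in the solo case. That is possible, but the allocation section distinguishes physician from clinic, and the GEE is specified for patients of the same physician. An analyst following the text would cluster on the wrong identifier. A separate analysis plan is not a full answer either, because the article does not leave the unit open; it states it in two incompatible ways.

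**Size.** This objection largely stands. The 6.8% to 8.6% needs every patient to sit in a four-physician, four-patient clinic at an assumed ICC. The primary outcome is a prescribing act, so correlation between patients of different physicians may be weaker than within one physician. The documents give no figure either way.

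**Where the error sits.** In that extreme case the inflation belongs to the primary chi-square as much as to the physician-level GEE. Changing the cluster identifier in the sensitivity analyses alone would leave the primary test as it is. This stands and shapes the fix.

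**Sample size.** A reader might infer that the margin of 22 rests on cluster sizes that are too small and that the trial is underpowered. The documents do not support that. Sample size derives the margin from no cluster size, ICC or loss rate, and 160 per arm is enough under several plausible combinations in the table. Figures such as 74% power at a design effect of 1.2, or 68% at 1.4, need an assumed 10% loss as well as those design effects.

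**Conclusion.** The mismatch is in the text and needs no assumption: practices are randomised, while the design-effect argument and both clustering analyses are defined by physician. These analyses under-correct wherever a group clinic contributes patients of more than one physician and within-clinic correlation is positive.

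The size cannot be fixed from the documents. Type I error ranges from close to the nominal 5% to 6.8% to 8.6% in the four-physician illustration. That illustration is not an estimate for this trial, nor a strict ceiling, since larger clinics would give more.

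On power, 160 per arm keeps 80% up to a design effect of about 1.16 with no loss, 1.10 with 5% loss and 1.04 with 10% loss. Whether that suffices cannot be judged from patients per physician. The margin is justified on the wrong unit; it is not shown to be inadequate. This should be fixed, but it does not by itself undermine the trial.

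**What to change.** 1. Name the practice, as defined in Allocation to experimental arms, as the unit of allocation throughout: Abstract, Allocation to experimental arms and Statistical analyses.
2. Use the randomised practice ID as the GEE cluster and as the unit of the cluster-level analysis.
3. Let the practice-clustered result, not the unadjusted chi-square alone, support the primary conclusion.
4. Base the design effect on expected patients per practice, with allowance for unequal sizes, over a stated ICC range. Restate the power that 160 per arm gives after a stated loss rate.

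The cost is mostly wording. The randomisation software must already recognise each practice in order to assign its later patients, so no new data are needed. The downside is slightly wider intervals and possibly a less favourable stated power.
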